## Abstract

**Background:**

Recently, excellent results are reported on laparoscopic lavage in patients with purulent perforated diverticulitis as an alternative for sigmoidectomy and ostomy.

The objective of this study is to determine whether LaparOscopic LAvage and drainage is a safe and effective treatment for patients with purulent peritonitis (LOLA-arm) and to determine the optimal resectional strategy in patients with a purulent or faecal peritonitis (DIVA-arm: perforated DIVerticulitis: sigmoidresection with or without Anastomosis).

**Methods/Design:**

In this multicentre randomised trial all patients with perforated diverticulitis are included. Upon laparoscopy, patients with purulent peritonitis are treated with laparoscopic lavage and drainage, Hartmann's procedure or sigmoidectomy with primary anastomosis in a ratio of 2:1:1 (LOLA-arm). Patients with faecal peritonitis will be randomised 1:1 between Hartmann's procedure and resection with primary anastomosis (DIVA-arm). The primary combined endpoint of the LOLA-arm is major morbidity and mortality. A sample size of 132:66:66 patients will be able to detect a difference in the primary endpoint from 25% in resectional groups compared to 10% in the laparoscopic lavage group (two sided alpha = 5%, power = 90%). Endpoint of the DIVA-arm is stoma free survival one year after initial surgery. In this arm 212 patients are needed to significantly demonstrate a difference of 30% (log rank test two sided alpha = 5% and power = 90%) in favour of the patients with resection with primary anastomosis. Secondary endpoints for both arms are the number of days alive and outside the hospital, health related quality of life, health care utilisation and associated costs.

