In case of faecal peritonitis there is no evidence that LL is a valid alternative for a resectional strategy. But again, the optimal surgical treatment is still a matter of debate. The available literature suggests equality of Hartmann's procedure (HP) and resection with primary anastomosis (PA) regarding postoperative mortality and morbidity[5,8,9,23,24]. The likelihood of stoma closure seems higher after PA with ileostomy (85%) compared to HP (60%), but robust evidence is lacking[13,25]. Therefore, HP and PA are compared to determine the optimal resectional treatment for perforated diverticulitis with generalised purulent or faecal peritonitis, regarding stoma free survival (DIVA-arm).

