### Study objectives

For this two-armed randomised trial two objectives can be defined to determine the optimal strategy for the treatment of perforated diverticulitis. First, is laparoscopic lavage for patients with purulent peritonitis superior compared to sigmoidectomy, in terms of mortality, morbidity, quality of life, health care utilisation and associated costs (LOLA-arm)? Secondly, is HP or PA the superior approach for patients with purulent or faecal generalised peritonitis in terms of stoma free survival, quality of life and cost-effectiveness (DIVA-arm)?

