**Figure 1 F1:**
[figure not shown]
**Study profile**.

In case of purulent peritonitis (Hinchey III) patients are randomised to LL, HP or PA (LOLA-arm). The best evidence indicates that the latter two resectional strategies are equal in terms of postoperative morbidity and mortality in case of generalised peritonitis[8]. For this reason a three way 2:1:1 randomisation is performed. In case of an overt perforation with faecal peritonitis (Hinchey IV) patients will undergo laparotomy and are randomised 1:1 to either undergo HP or PA.

Patients who are either ineligible for trial entry, who show other causes of peritonitis than diverticulitis at laparoscopy or who do not wish to take part in the study are treated at the discretion of the surgeon on call. These patients will be registrated by the trial coordinator.

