## List of abbreviations

LOLA-arm: Laparoscopic lavage and drainage or sigmoidectomy with HP or PA for purulent peritonitis for perforated diverticulitis; DIVA-arm: Sigmoidectomy with HP or PA for generalised peritonitis for perforated diverticulitis; SF-36: Quality of Life Questionnaire Short Form 36; GIQLI: Gastro Intestinal Quality of Life Index; EQ-5D: Euro Quality of Life Questionnaire; LL: Laparoscopic lavage; HP: Hartmann's procedure; PA: Sigmoidectomy with primary anastomosis.

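### The DIVA-arm is faecal peritonitis only where it is labelled and sized in the abstract, but purulent or faecal elsewhere, so its primary population and the trial total (344 or 476) are inconsistent

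*Protocol article*

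**What the plan says.** All references are to the protocol article.

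**Faecal only.** Abstract, Methods/Design: "Patients with faecal peritonitis will be randomised 1:1" between HP and PA, and this allocation alone carries the DIVA label. The same paragraph then gives the DIVA endpoint and says that 212 patients are needed in this arm. The text accompanying Figure 1 gives the purulent patients the other label alone, including those allocated to HP or PA: "In case of purulent peritonitis (Hinchey III) patients are randomised to LL, HP or PA (LOLA-arm").

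**Purulent or faecal.**
- Abstract, Background: "to determine the optimal resectional strategy in patients with a purulent or faecal peritonitis (DIVA-arm".
- Background, last paragraph: "perforated diverticulitis with generalised purulent or faecal peritonitis, regarding stoma free survival (DIVA-arm").
- Study objectives: "is HP or PA the superior approach for patients with purulent or faecal generalised peritonitis in terms of stoma free survival".
- List of abbreviations: "DIVA-arm: Sigmoidectomy with HP or PA for generalised peritonitis for perforated diverticulitis", with no restriction by type of peritonitis.
- The Discussion part of the abstract also speaks of the best resection strategy for both types.

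**Sample size.** The Statistical analysis section gives 132:66:66 for LOLA and 212 for DIVA as two separate figures. It gives no trial total and does not say whether the two sets of patients overlap.

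**The concern.** DIVA is one of the trial's two primary comparisons, and the article gives it two different populations. The choice settles three things: which patients enter the stoma-free survival analysis, which patients its conclusion applies to, and how many patients must be recruited. The two parts of the abstract that disagree follow one another directly.

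This goes beyond detail that a short article leaves to a fuller document, because the printed statements contradict each other on who is analysed. If the point stays open, the primary population could be settled after results are known.

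**Working it through.** **1. Inputs**
- LOLA: 132:66:66, so 264 patients, of whom 66 + 66 = 132 are allocated to resection. Planning rates are 25% v 10%, two-sided 5%, power 90% (Abstract, Methods/Design; Statistical analysis).
- DIVA: 212 patients, log-rank test, two-sided 5%, power 90%. Reversal rates after correction for mortality are 50% (HP) and 72% (PA) (Statistical analysis).

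**2. Do the stated sample sizes reproduce?** Take (1.960 + 1.282)² = 10.507.
- *LOLA, likelihood ratio test.* Let H(p) = p ln p + (1−p) ln(1−p). Then n per group = 10.507 / {2[H(0.25) + H(0.10) − 2H(0.175)]} = 10.507 / 0.0801 = 131.2, rounded up to 132, so 264 in all. The usual two-proportion formula gives 133 per group, or 266. The stated 264 is confirmed.
- *DIVA, log-rank (Freedman).* HR = ln 0.72 / ln 0.50 = 0.474. Events = 10.507 × [(1 + 0.474)/(1 − 0.474)]² = 82.5. The mean event proportion is 1 − (0.50 + 0.72)/2 = 0.39. N = 82.5/0.39 = 211.5, or 212.8 if events are first rounded up to 83. The stated 212 is confirmed.

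The 212 therefore fits 50% v 72%. The abstract's 30% difference is a separate inconsistency and does not bear on this point. The calculation uses one pair of rates and contains nothing specific to faecal or purulent disease, so it cannot show which population was meant.

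**3. Trial total under each reading**

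| Reading of DIVA | Faecal patients needed | Trial total |
|---|---|---|
| Purulent or faecal, LOLA resections counted | 212 − 132 = 80 | 264 + 80 = 344 |
| Faecal only | 212 | 264 + 212 = 476 |

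The gap is 476 − 344 = 132 patients. The pooled reading is arithmetically coherent: 66 from LOLA plus 40 faecal gives 106 per resection group, which is 212 / 2.

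**4. Which reading has more support?** Every statement of DIVA's purpose covers both types of peritonitis. The faecal-only reading rests on one label in the abstract and the sentence that attaches 212 to it, supported indirectly by the LOLA-only label on purulent patients beside Figure 1. The body text on faecal randomisation carries no DIVA label. The pooled reading is the more probable intention, but no readable sentence states the overlap.

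**The case against.** The strongest reply is that the intention is clear enough. The objective, the rationale and the abbreviation list agree, and the outlier is a parenthesis in a condensed abstract. Figure 1, to which the article refers for the randomisation, may show the LOLA resection patients feeding into DIVA. Much of this stands. It makes the pooled reading the better supported one, and the missing figure limits how firmly one can say that the overlap is unstated. It does not remove the contradictory label, and the statistical section still does not say whom the 212 comprise.

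Stronger conclusions that a reader might draw are not supported:
- *That DIVA is underpowered because only about 80 faecal patients would be recruited.* This joins the population of one reading to the recruitment of the other. Under either reading followed consistently, 212 patients are analysed and the planned power applies.
- *That pooling biases the comparison.* HP:PA is 1:1 within the 2:1:1 allocation and within the 1:1 allocation, so type of peritonitis is not confounded with treatment.
- *That purulent and faecal patients differ in their chance of stoma-free survival.* The article gives no rates by Hinchey grade.
- *That stopping LOLA early would undermine DIVA.* Under the pooled reading 132/212 = 62% of DIVA comes through LOLA, but the article does not say what would then happen to HP and PA randomisation. That may be settled in documents not shown, and no rule is proposed here.

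**Conclusion.** The point holds as an internal inconsistency about the population of a primary analysis. The size of the ambiguity is 132 patients: a total of 344 if the LOLA resection patients are shared with DIVA, and 476 if they are not.

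These totals assume that LOLA recruits exactly 264 patients, that under the pooled reading all 132 of its resection patients count towards DIVA, and that no allowance is made for dropout (none is stated). Neither sample size is wrong in itself. The purulent-or-faecal reading is clearly the better supported, subject to what Figure 1 shows. The matter should be corrected because it fixes who is analysed and what the result covers, but it does not show that the trial is underpowered or biased.

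**What to change.** 1. Correct the Methods/Design part of the abstract, and the label in the text accompanying Figure 1, to match the stated objective: DIVA is all patients randomised to HP or PA, Hinchey III (through the LOLA allocation) and Hinchey IV.
2. State in the Statistical analysis section that the 212 include the planned 132 LOLA resection patients, leaving about 80 further faecal patients and a trial total of about 344 before any dropout allowance.
3. If faecal peritonitis only is intended, change the objective, the rationale and the abbreviation list instead, and state the total of 476.
4. Optionally, analyse the pooled DIVA comparison stratified by Hinchey grade, since grade already determines which randomisation a patient enters. This is a small gain in precision and not a correction for bias. The article gives no rates by grade from which to size it.

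Under the pooled reading, items 1 and 2 cost wording only and item 4 costs no patients. Under the faecal-only reading, the cost is an explicit commitment to 132 more patients than the pooled total.

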**Discussion:**

The Ladies trial is a nationwide multicentre randomised trial on perforated diverticulitis that will provide evidence on the merits of laparoscopic lavage and drainage for purulent generalised peritonitis and on the optimal resectional strategy for both purulent and faecal generalised peritonitis.

**Trial registration:**

Nederlands Trial Register NTR2037

## Background

Diverticular disease is an important condition in terms of healthcare utilisation and it is one of the five most costly gastrointestinal disorders in westernised countries[1]. Despite this high prevalence, treatment of all different stages of diverticular disease is still hardly evidence based, hence containing a lot of controversies.

Perforated diverticulitis is a perforation of an inflamed diverticulum of the large bowel, mostly the sigmoid, resulting in either purulent or faecal peritonitis (Hinchey stadia III or IV). Both conditions require emergency surgery[2,3]. Regardless of selected strategy emergency operations for acute perforated diverticulitis are associated with substantial morbidity (up to 50%) and mortality (15 to 25%)[3-8]. Primary sigmoidectomy with or without anastomosis has become the standard practice for patients with generalised peritonitis complicating diverticulitis [6-10] and for many surgeons the Hartmann's procedure remains the favoured option. Restoration of bowel continuity after this procedure is a technically difficult operation, with high morbidity and mortality rates[11,12]. Therefore stoma reversal after HP is only performed in 50 to 60% of the patients, thereby compromising quality of life and increasing costs[13,14].

Recently laparoscopic lavage (LL) emerged as an effective alternative for patients with perforated diverticulitis with purulent peritonitis[15]. This nonresectional procedure has first been described by O'Sullivan in 1996[16]. In 2009, a systematic review on all studies on laparoscopic lavage with a total number of 231 patients was performed. Mortality was less than 2% and a (permanent) colostoma was avoided in the majority of these patients[15-22]. So laparoscopic lavage for perforated purulent diverticulitis has a great potential in improving health and reducing costs.

Nevertheless, since sigmoidectomy is still considered the standard of care for perforated diverticulitis, implementation of LL might be variable. Some surgeons will embrace lavage because of its technical simplicity; other might be reluctant fearing failure of this novel strategy. Only a head to head comparison of both surgical strategies will provide an evidence based surgical approach of patients with perforated diverticulitis with purulent peritonitis (LOLA-arm).

In case of faecal peritonitis there is no evidence that LL is a valid alternative for a resectional strategy. But again, the optimal surgical treatment is still a matter of debate. The available literature suggests equality of Hartmann's procedure (HP) and resection with primary anastomosis (PA) regarding postoperative mortality and morbidity[5,8,9,23,24]. The likelihood of stoma closure seems higher after PA with ileostomy (85%) compared to HP (60%), but robust evidence is lacking[13,25]. Therefore, HP and PA are compared to determine the optimal resectional treatment for perforated diverticulitis with generalised purulent or faecal peritonitis, regarding stoma free survival (DIVA-arm).

### Study objectives

For this two-armed randomised trial two objectives can be defined to determine the optimal strategy for the treatment of perforated diverticulitis. First, is laparoscopic lavage for patients with purulent peritonitis superior compared to sigmoidectomy, in terms of mortality, morbidity, quality of life, health care utilisation and associated costs (LOLA-arm)? Secondly, is HP or PA the superior approach for patients with purulent or faecal generalised peritonitis in terms of stoma free survival, quality of life and cost-effectiveness (DIVA-arm)?

## Methods/Design

The Ladies trial is designed as a nationwide multicentre randomised trial in which patients with generalised peritonitis caused by perforated diverticulitis are randomised to undergo either laparoscopic lavage and drainage or resectional surgery by laparotomy.

Patients presenting with clinical signs of diverticulitis with diffuse peritonitis can be included upon the finding of free gas on plain abdominal radiography, upon the finding of free gas on CT, or upon the finding of peritonitis with diffuse fluid or gas on CT. Exclusion criteria include dementia, pelvic irradiation, steroid treatment, prior sigmoidectomy and preoperative shock with inotropic requirement. All patients need to fulfil the selection criteria and will need to give written informed consent.

Eligible patients undergo diagnostic laparoscopy to exclude other causes of generalised peritonitis. If the diagnosis perforated diverticulitis is confirmed, the patient can be enrolled and randomised. Block-randomisation is performed during laparoscopy via the trial website according to Figure 1.

**Figure 1 F1:**
[figure not shown]
**Study profile**.

In case of purulent peritonitis (Hinchey III) patients are randomised to LL, HP or PA (LOLA-arm). The best evidence indicates that the latter two resectional strategies are equal in terms of postoperative morbidity and mortality in case of generalised peritonitis[8]. For this reason a three way 2:1:1 randomisation is performed. In case of an overt perforation with faecal peritonitis (Hinchey IV) patients will undergo laparotomy and are randomised 1:1 to either undergo HP or PA.

Patients who are either ineligible for trial entry, who show other causes of peritonitis than diverticulitis at laparoscopy or who do not wish to take part in the study are treated at the discretion of the surgeon on call. These patients will be registrated by the trial coordinator.

### Endpoints

Primary endpoint of the LOLA-arm is the combined number of mortality and major morbidity, twelve months after initial surgery. Secondary endpoints of the LOLA-arm are quality of life, health care utilisation and associated costs. Mayor morbidity includes reintervention, fascial dehiscence, incisional hernia, myocardial infarction, urosepsis, respiratory failure and renal failure. Respiratory failure is defined as a SOFA score of less than 300. Renal failure is defined as a threefold creatinine increase or a GFR decrease over 75% or a urinary output of less than 0.3/kg/h for 24 hours or anuria for twelve hours.

Primary endpoint of the DIVA-arm is the stoma free survival within twelve months after initial surgery. Secondary endpoints are quality of life and cost-effectiveness.

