### Statistical analysis

The analysis will be performed in accordance with the intention to treat principle.

In the LOLA-arm of the study, the assumpted difference in the combined number of mortality and major morbidity between laparoscopic lavage and resection is 15%. With a two sided likelihood ratio test and a significance level of 0.05, a sample size of 132:66:66 will be necessary to detect this difference. With a group size of a hundred patients per arm it is also possible to find a significant difference (alpha = 0.05, beta = 0.1) of at least 10% in subscales of the SF-36, a validated quality of life questionnaire, at two, four, thirteen, 26 and 52 weeks after initial surgery.

In the DIVA-arm 212 patients are needed to significantly demonstrate a difference in stoma free survival between both treatment arms, using log rank statistics with a power of 90% and a type I error of 5%. The suspected postoperative mortality for HP and PA is equally high (+ 15%)[8]. About 60% of the patients that underwent HP have their stoma reversed[11,12]. When corrected for the expected mortality before reversal, the reversal rate will be 50%. Patients with a protective loop-ileostomy after PA will have their enterostomy reversed in over 85%[12]. After correction for expected mortality before reversal, this will result in a 72% stoma reversal rate in the initial patient population.

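### Respiratory failure, one of seven major-morbidity components of the LOLA primary endpoint, is defined by a score and a threshold that cannot belong together

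*Protocol article*

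**What the plan says.** The Endpoints section sets the LOLA outcome: "Primary endpoint of the LOLA-arm is the combined number of mortality and major morbidity, twelve months after initial surgery". It then lists what counts as major morbidity: "Mayor morbidity includes reintervention, fascial dehiscence, incisional hernia, myocardial infarction, urosepsis, respiratory failure and renal failure". Two of the seven components get an operational definition there. Renal failure has several criteria, based on creatinine, GFR and urine output. Respiratory failure has one: "Respiratory failure is defined as a SOFA score of less than 300".

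SOFA is mentioned nowhere else in the article, so no other section corrects or qualifies this sentence. The Abstract (Methods/Design) repeats the endpoint without defining its components: "The primary combined endpoint of the LOLA-arm is major morbidity and mortality". It plans on a fall in the event rate "from 25% in resectional groups compared to 10% in the laparoscopic lavage group".

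**The concern.** A threshold of 300 does not fit a SOFA score. SOFA is a small ordinal organ-failure score on which a higher value means more dysfunction. A rule that counts low values, with a cut-off far above the top of the scale, cannot identify respiratory failure.

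The article does not leave this definition to a fuller document. It states a definition, and the definition is wrong. The renal criteria beside it show that component definitions were meant to be operational.

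At stake is how a component of the primary endpoint is counted. A reader or local investigator must work out which variable was meant, in which unit and at which level, and different people may decide differently. The neighbouring urine-output criterion has a smaller gap of the same kind: it gives 0.3 per kg per hour without a volume unit.

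**Working it through.** **Inputs**
- Definition, component list and composite: Endpoints.
- Planned rates 25% (resection) and 10% (lavage), two-sided alpha 5%, power 90%: Abstract, Methods/Design.
- Test and size: Statistical analysis, "With a two sided likelihood ratio test and a significance level of 0.05, a sample size of 132:66:66 will be necessary". The two resection groups together give 66 + 66 = 132, so the comparison is 132 v 132.
- Range of SOFA: not in the document. Assumed 0 to 24 in total and 0 to 4 per organ, higher being worse.

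**Step 1. The plan's own figure.** For a likelihood ratio test with equal groups and mean rate p = (0.25 + 0.10)/2 = 0.175:

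d = 2 × [0.25 ln(0.25/0.175) + 0.75 ln(0.75/0.825) + 0.10 ln(0.10/0.175) + 0.90 ln(0.90/0.825)] = 2 × (0.0892 − 0.0715 − 0.0560 + 0.0783) = 0.0801

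n = (1.960 + 1.282)² / d = 131.2, rounded up to 132 per group.

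Exact enumeration of this test at 132 v 132 gives power 90.7%. The usual normal approximation without continuity correction gives 89.8%. The planned size reproduces, and nothing below changes it.

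**Step 2. The definition taken literally.** The highest possible SOFA total is 24, or 4 for a single organ. Both are below 300, so the component is met with probability 1 in every group. A composite is met when any component is met, so the endpoint rate becomes 100% v 100%, the difference is 0, and no effect can be detected. The exact range does not matter, because any maximum below 300 gives the same result.

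**Step 3. Is it only a reversed sign?** No. With the inequality turned round, a score above 300 is impossible and no patient would meet the component. Neither direction discriminates, so the named variable itself does not match the threshold.

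**Step 4. What can be said about a realistic effect.** Misclassifying this component changes a patient's endpoint status only if the patient has not died and has none of the other six components. The article gives no rate for any component and no overlap between them, so that share is unknown and the effect cannot be derived.

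The following shows only how the design responds to spurious events. Suppose, purely as an assumption, that loose classification adds a false event independently in a share q of patients in both groups. The rates become 0.25 + 0.75q and 0.10 + 0.90q, and the difference shrinks to 0.15(1 − q). By the normal approximation at 132 v 132:

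| q (assumed) | Resection | Lavage | Power |
|---|---|---|---|
| 0 | 25.0% | 10.0% | 90% |
| 5% | 28.8% | 14.5% | 81% |
| 10% | 32.5% | 19.0% | 71% |
| 25% | 43.8% | 32.5% | 47% |

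No value of q comes from the document, and missed events are as conceivable as added ones. The table is not an estimate for this trial.

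**The case against.** The best defence is that nobody would apply the sentence as printed. Clinicians would not record respiratory failure in a patient who is breathing normally, and many would recognise 300 as a value from an oxygenation measure. The Patient safety section also describes an independent monitor, a central online database, and training of personnel on the protocol and data entry. The case report form is not shown and may already hold the right wording. Only one of seven morbidity components is affected.

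Most of this stands, and it limits the point. A reader might infer from the literal definition that the trial has no power. The document does not support that as a forecast, because it requires a use of the rule that is unlikely. Variation between centres is likewise a risk that the wording creates, not something the article shows to have happened.

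A reader might also infer that, with no time limit in the definition, respiratory failure present before or during the operation would count. The document does not support this either. The Endpoints section ties the outcome to the year after the first operation, the Data collection and monitoring section has complications assessed from week four to week 52 after that operation, and it records the preoperative state separately through the APACHE score. Finer timing is commonly left to the full protocol. A third inference, that outcome assessors knew the treatment and would err differently by group, also lacks support, since the article is silent on assessor blinding.

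The defence does not rescue the sentence. Guessing the intended variable is not the same as having it stated with its unit, and the training described would be on a protocol whose published definition cannot work.

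**Conclusion.** The concern holds as an error in the wording of a primary-endpoint component. As printed, the definition of respiratory failure is met by every patient and runs against the direction of the score. This rests on the assumed SOFA range, but needs only a maximum below 300 and a scale on which higher is worse. That 300 refers to an oxygenation quantity behind the respiratory item is probable, but the article does not say so.

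The practical consequence is possible inconsistent classification of one component among the participating hospitals. Its size cannot be quantified from the document. The figure of 100% v 100% describes the literal rule, not an expected result. The sample size of 132:66:66 reproduces and is not in question.

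**What to change.** Correct the sentence in Endpoints so that it names the variable and unit to which the threshold applies, or else the corresponding level of the respiratory SOFA item. The sponsor must say which was intended; this review proposes no threshold. Check the corrected sentence against the full protocol and the case report form so that all centres use one definition. In the same paragraph, add the missing volume unit to the urine-output criterion for renal failure.

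If the full protocol and case report form already have the right wording, only the published text needs correcting. If they do not, the form needs the same change, and respiratory events already recorded should be checked against the corrected definition. The correction itself is one sentence and one unit, and needs no additional patients and no change to the sample size.
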